#### Participant incentives

Participants will receive an electronic gift card by email following completion of the baseline measures battery (US $20), post-intervention measures battery (US $20), and interview (US $25).

### Measures

#### Sociodemographic and medical variables

The following sociodemographic information will be collected via a brief background/demographic questionnaire and medical chart abstraction: participant age, sex assigned at birth, gender identity, race, and ethnicity. We will also collect data on participants’ current residence’s distance from SCH and whether they relocated to the Seattle area for treatment. The following disease- and treatment-related variables will be collected via medical chart abstraction: diagnosis, age at diagnosis, months/years since diagnosis, active treatment vs off treatment, months/years since treatment completion, and type(s) of treatment received (e.g., chemotherapy, radiation, surgery, HSCT).

#### Feasibility (Aim 1)

Feasibility will be assessed by the number of patients enrolled, session attendance, and attrition. Feasibility will be defined as ≥ 5 AYAs enrolled in each group offered, attendance ≥ 60% of sessions, and < 25% attrition (i.e., number of AYAs who withdraw from group). Reasons for dropout will be noted. Evidence indicates that ideal group size for group interventions depends on the target population, but that five or more members allow for meaningful relationships to form and for group cohesion to develop [29]. Our target numbers for feasibility are also informed by prior clinical experience and reflect the reality that some group members are on active treatment and have medical events that may interfere with group participation at times. We take these metrics into consideration when defining feasibility of the intervention given the unique challenges and needs of this population. We also anticipate that AYAs who are only able to attend 60% of sessions may still find the intervention to be acceptable/satisfactory. For patients who were referred to group but did not enroll, the reason for not enrolling (e.g., no longer interested, schedule conflict) will be noted in the referral in the electronic medical record when the scheduling team contacts the patient/family to enroll in the group.

#### Acceptability (Aim 1)

Acceptability of the telehealth group intervention will be assessed by an internally developed measure used widely within SCH to evaluate group-based interventions as part of routine measurement-based care. It was adapted from the Client Satisfaction Questionnaire (CSQ), which has excellent internal consistency and solid psychometric properties [30]. The CSQ has also been used among cancer populations, including adolescent and young adult cancer survivors [31, 32]. All changes made to the CSQ were to reduce respondent burden and tailor questions to specific clinical programs. This questionnaire was further adapted and modified for relevance to the High School Cancer Group and AYA Cancer Group. There are 16 items that assess group acceptability (i.e., group satisfaction) and telehealth acceptability. A threshold of 80% for acceptability ratings will be used as an indicator of intervention acceptability. This measure takes less than 10 min to complete.

#### Semi-structured patient interviews (Aim 2)

A semi-structured interview was developed for this study. Patient interviews will assess perceived benefits (including potential impact on social isolation and connectedness, sense of community, and psychological well-being), barriers/challenges, telehealth group acceptability, and suggestions for intervention refinement. It is anticipated that interviews will last approximately 30–45 min. Study staff will be trained by the first author ([name]) and complete mock interviews prior to conducting interviews with participants. A copy of the interview guide is available from the first author upon reasonable request.

#### Patient-reported outcomes (Aim 3)

##### Revised UCLA Loneliness Scale

Participants will complete the Revised UCLA Loneliness Scale [33]. This 20-item self-report measure assesses social isolation (or lack of social connectedness). Sample items include the following: “I feel left out,” “I feel isolated from others,” “I have a lot in common with the people around me,” “There are people who really understand me,” and “There are people I can talk to.” Items are rated on a 4-point Likert scale (1 = never, 4 = often). Certain items are reverse scored. This widely used measure has demonstrated validity and reliability among adolescents and young adults.

##### *PROMIS* Depression Short Forms

Participants will complete the *PROMIS* Emotional Distress — Depression Short Form [34] (ages 18 years and above) or the *PROMIS* Pediatric Depression Short Form [35] (ages < 18 years). This 8-item self-report questionnaire assesses depressive symptoms in the past 7 days. Sample items on the adult form include the following: “I felt worthless,” “I felt helpless,” and “I felt depressed.” Sample items on the pediatric form include the following: “I felt sad,” “I was less interested in doing things I usually enjoy,” and “It was hard for me to have fun.” Items are rated on a 5-point Likert scale (1 = never, 5 = always). This measure takes approximately 2 min to complete. These *PROMIS* measures have demonstrated validity and reliability [34–36].

##### Benefit Finding/Burden Scale for Children

Participants will complete the Benefit Finding/Burden Scale for Children [37, 38]. This 20-item self-report measure assesses perceived benefit and burden associated with a specified event. For this study, we will examine the 10-item Benefit Finding subscale, which assesses one’s perception of personal growth resulting from an identified event. Sample items include the following: Having my illness… “has helped me become a stronger person,” “has helped me learn to deal better with my problems,” and “has taught me what is really important in life.” Items are rated on a 5-point Likert scale (“Not at all true for me” to “Very true for me”). This is a well-validated measure with excellent internal reliability that has been used in studies of children, adolescents, and young adults with cancer [39, 40].

### Analytic approach

Missing data will be examined and handled following best practices depending on the amount of missing data and patterns of missingness (e.g., pairwise deletion). We will include descriptives of patient demographic and disease characteristics to examine whether there are any obvious commonalities in dropout and to directly query and catalog reasons for dropout when possible. Data from participants in the AYA Cancer Group and the High School Group will be combined and analyzed together.

Data will be summarized using descriptive statistics in SPSS. For Aim 1, to assess feasibility and acceptability, the following metrics and descriptive statistics will be calculated: number of AYAs enrolled in each group (target: ≥ 5 AYAs per group), number of sessions attended (target: ≥ 60% of sessions), and attrition (target: < 25%). The number of AYAs referred to group who did not enroll and frequencies of their reasons for not enrolling will also be calculated. Acceptability ratings will be calculated with a target of 80% as an indicator of intervention acceptability.

For Aim 2, we will conduct a qualitative content analysis of interview data to assess patient experience and feedback in Dedoose, a web application for analyzing qualitative and mixed methods research (www.dedoose.com). We will develop an a priori codebook based on questions from the interview guide. At least two independent coders will code interview transcripts, and discrepancies will be resolved through discussion to reach consensus utilizing constant comparative methods [41, 42].

For exploratory Aim 3, scores for social isolation/social connectedness, depressive symptoms, and benefit-finding pre- and post-intervention will be computed, and simple descriptive statistics will be calculated. Because this is a feasibility pilot study that is not powered to detect significant outcomes, we will not conduct formal directional hypothesis testing [43, 44]. However, we plan to conduct paired samples *t*-tests to evaluate changes in scores from pre- to post-intervention in an exploratory manner. Exploration of preliminary efficacy will inform sample size and power of future trials.

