**Discussion:**

Findings from this pilot study will inform intervention refinement, intervention implementation, and sample sizes for future powered trials. This study will provide preliminary empirical evidence to support the development of effective group interventions for AYAs with cancer that increase opportunities for social interaction and access to peer support, with the potential to contribute to improved psychosocial care of AYAs with cancer.

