## Methods

### Setting and sample

We plan to recruit 20 participants who attend telehealth peer support groups at Seattle Children’s Hospital (SCH) in Fall 2023 and Spring 2024. If more than 20 AYA patients are eligible and express interest in research participation, we will select participants to ensure a representative and diverse sample. Our target sample size was determined based on empirical guidance on sample sizes for saturation in qualitative research [26] and group sizes that have ranged from 6 to 10 in prior years. Consistent with prior groups, it is expected that participants will represent a range of cancer and brain tumor diagnoses and include patients both on and off treatment. Participants’ race and ethnicity are expected to reflect that of the larger patient population served in the Cancer and Blood Disorders Center at SCH. The projected gender, racial, and ethnic composition represents the demographics of Washington state. It is expected that the majority (up to 70%) of AYA participants will be White, ~ 12% Hispanic/Latino, ~ 4% Black/African American, and ~ 8% Asian. Approximate sex composition based on prior enrollment rates from the Cancer and Blood Disorders Center outpatient clinic at SCH is 43% female and 57% male.

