This study has several limitations as well as potential practical and operational challenges and considerations. First, this is a small, single-site pilot study without a comparison group, and generalizability of findings for a single-site study is limited. Recruiting a diverse sample may also be challenging. Nonetheless, this study is an important first step and will serve as formative groundwork for future studies to test this intervention in a multi-site randomized controlled trial. Second, groups will include a heterogeneity of diagnoses and treatment phases; sample size will prohibit meaningful examination of potential differences across diagnoses and treatment phases. This will be important to examine in future larger studies. Diversity of experiences may be beneficial as this group intervention is intended to be broadly applicable to AYAs with cancer on and off treatment. Third, groups are limited to English-speaking participants. Active efforts are underway at our institution to obtain simultaneous interpretation for group interventions. Fourth, because AYAs self-select into groups, this may affect the representativeness of our sample, and this study carries risk of selection bias. We will not be able to collect data (e.g., feedback about barriers, reasons for nonparticipation) for AYAs who are not interested or referred to the group. This is another important future direction for research. We will track reasons for nonparticipation for AYAs who are referred to group but decline/do not enroll. Additionally, patients’ lack of awareness of availability of behavioral health services is often a barrier to receiving services. Some patients and families may not be aware of groups (e.g., patients who are seen less frequently at SCH, are further out from treatment, or who may be viewed by providers as less likely to want to participate in a group) precluding their participation, which may also affect representativeness of participants. Strong efforts will be made to increase patient and family awareness of the availability of the groups. Fifth, some group members have enrolled in prior cycles of group and are considered “repeaters,” which may also contribute to selection bias. As such, their baseline is not a true baseline. We will take this into consideration as we analyze the data. This observation suggests that some AYAs find continued benefit from the intervention prompting them to repeat group participation, which has interesting and important clinical implications. Finally, use of the adapted internally developed measure of acceptability was a pragmatic decision and includes items that assess both intervention acceptability and satisfaction. A future direction is to more clearly measure these constructs separately, such as by adapting the theoretical framework of acceptability questionnaire to assess acceptability of our telehealth group intervention for AYAs with cancer at the current and other treatment centers [48].

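### The uncontrolled pre-post change in a target of 20 participants should not set the target difference of the future randomised trial

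*Protocol article*

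**What the plan says.** The Analytic approach section of the protocol article says that Aim 3 scores will first be summarised descriptively. Because the pilot is not powered, "we will not conduct formal directional hypothesis testing [43, 44"], but paired t-tests of pre-to-post change will be run in an exploratory way. The paragraph ends: "Exploration of preliminary efficacy will inform sample size and power of future trials". The Discussion paragraph of the Abstract repeats this purpose, saying that the findings will inform "sample sizes for future powered trials".

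On numbers, Setting and sample says: "We plan to recruit 20 participants who attend telehealth peer support groups". The figure acts as a ceiling: "If more than 20 AYA patients are eligible and express interest in research participation, we will select participants". Its basis is not statistical precision: "Our target sample size was determined based on empirical guidance on sample sizes for saturation in qualitative research", together with past group sizes of 6 to 10.

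The Discussion concedes that "this is a small, single-site pilot study without a comparison group" and that returning members lack a genuine baseline. It names a multi-site randomised controlled trial as a later step, and its last paragraph adds that this trial should be adequately powered. The Analytic approach pools the High School and AYA groups. The article does not mention correlation between members of the same group.

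**The concern.** The input named for future sample size is preliminary efficacy, that is, the effect estimate. The article does not name the SD, the pre-post correlation or the retention rate for this purpose. Two problems follow.

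- **Wrong quantity.** A randomised trial is sized on the difference between arms. A change without controls adds whatever would have happened anyway. Members choose to join, and referrers weigh their wish for social connection (Setting and sample), so some may enter at a low point and drift back towards their usual level. For returning members the first score is not a pre-treatment score.
- **Poor precision.** Twenty pairs leave the standardised change so uncertain that the trial sizes it implies run from very small to unbounded.

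A lesser point is that members of one group interact by design, and the Overview of group intervention treats cohesion as part of how the group works. Their changes may therefore be correlated, which a pooled paired t-test ignores.

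At stake is the next trial. If the pilot change guides its target difference, the trial could be too small to answer its question or needlessly large.

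**Working it through.** **Inputs from the article:** target of 20 pairs at most, one arm, paired t-tests, two group types (High School, AYA) over two cycles (Fall 2023, Spring 2024). The article does not state the number of groups; 2 × 2 = 4 is inferred.

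**Assumed, because the article gives no figures:** observed standardised change 0.40 (positive = improvement), two-sided 5%, 80% power, 1:1 allocation, pre-post correlation r = 0.5, group ICC 0.01 to 0.10. The target of 20 was not derived from a power formula, so there is no power calculation to reproduce, and 20 is not called wrong.

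**1. Precision of the change.** Half-width = t(0.975, 19)/√20 = 2.093/4.472 = 0.47 SD of change. This needs no assumed effect. For an observed 0.40, the exact noncentral-t 95% interval is -0.06 to 0.85.

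**2. Trial size implied.** A paired effect is in units of the SD of change, and SD of change = SD × √(2(1 − r)). At r = 0.5 the two SDs are equal, so the paired effect can enter the two-arm formula for post scores unchanged: n per arm = 2(1.960 + 0.842)²/d² = 15.70/d².

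| d used | n per arm |
|---|---|
| 0.85 (upper limit) | 15.70/0.7225 = 21.7, so 22 (23 with the t-based formula) |
| 0.40 (point estimate) | 15.70/0.16 = 98.1, so 99 |
| -0.06 (lower limit) | none; the effect has the wrong sign |

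The middle row depends on r. At r = 0.3, d = 0.40 × √1.4 = 0.473 and n = 71. At r = 0.7, d = 0.40 × √0.6 = 0.310 and n = 164.

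**3. Wrong quantity.** Suppose that the observed 0.40 includes 0.1 or 0.2 SD that untreated patients would also have gained (assumed, r = 0.5). The between-arm difference is then 0.30 or 0.20, and n per arm is 175 or 393 instead of 99. A larger pilot would not remove this error.

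**4. What the pilot can supply.** The 95% limits for the variance are 19/χ²(0.975, 19) = 19/32.85 = 0.58 and 19/χ²(0.025, 19) = 19/8.907 = 2.13 times its estimate. Required n is proportional to the variance, so even this input needs a range.

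**5. Clustering.** Take four groups of five. Design effect = 1 + (5 − 1) × ICC. The naive SE is too small by 1 − 1/√(design effect). The type I error of the nominal 5% paired t-test comes from simulation (100,000 runs).

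| ICC (assumed) | Design effect | Naive SE too small by | Type I error |
|---|---|---|---|
| 0.01 | 1.04 | 2% | 5.5% |
| 0.05 | 1.20 | 9% | 7.3% |
| 0.10 | 1.40 | 15% | 9.7% |

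Four groups cannot estimate the ICC. If it is truly 0.05, the central 95% of estimates runs from about -0.22 to 0.45.

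**The case against.** The strongest reply is that the article says that the results will inform sample size, not fix it. It labels both the aim and the tests exploratory, discloses the lack of power, the missing comparator and the repeat attenders, and claims no treatment effect. That stands against a harsher reading. A reader might infer that the next trial will be sized mechanically on one point estimate, or that the t-tests flatly contradict the refusal of formal directional testing. The text supports neither. The disclosed limits, however, are never applied to sample-size planning, which is where they matter most. An analysis plan not shown here could remove the stated use only by contradicting the sentence.

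A reader might also infer that the analysis is confined to completers and biased by illness. The article does not support this. Missing data are to be "handled following best practices depending on the amount of missing data and patterns of missingness (e.g., pairwise deletion"), so pairwise deletion is only an example. Illness is linked to missed sessions, whereas the questionnaires are completed remotely within three months, with reminders and follow-up (Data collection). No missing-data point is made here.

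On clustering, the objection is largely right. The ICC is not in the documents, the number of groups is inferred, and at 0.01 the effect is negligible. Nor does reporting by group adjust for it. Finally, a 95% interval carries the same information as the paired t-test, so dropping p-values changes presentation and not inference.

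**Conclusion.** The point holds for the stated use of the estimate. An uncontrolled change in at most 20 people is the wrong quantity for sizing a randomised trial, and its half-width of 0.47 SD makes it a poor guide in any case. The half-width follows from n = 20 alone. The per-arm figures illustrate the consequence and rest on the assumed change of 0.40, 80% power and r = 0.5; at the point estimate they move between 71 and 164 for r from 0.3 to 0.7. Clustering is secondary and conditional on the ICC. The conclusion does not extend to the target of 20 itself, which has a qualitative rationale, or to Aims 1 and 2.

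**What to change.** Replace the closing sentence of the Analytic approach, and align the Abstract, along these lines: *The observed pre-post change will not be used to set the target difference of a future randomised trial. The pilot will supply the SD, the pre-post correlation, and questionnaire completion and retention rates, each with its uncertainty. The target difference will be based on a minimal important difference, and sample size will be shown over a range of assumed group ICCs.* The articles and documents at hand give no minimal important difference, so the sponsor would need to justify one when the trial is designed.

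Report Aim 3 as mean change with 95% confidence interval and no p-value, pooled and by group. State that the pooled intervals do not account for clustering in what appear to be four groups, and that four groups are too few to estimate the ICC.

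The cost is wording and table layout: no extra participants, visits or data. The sponsor gives up p-values from tests that it already says are not powered.

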## Discussion

Adolescents and young adults with cancer have unique psychosocial needs, and their opportunities to connect with peers with cancer are limited. Telehealth group interventions for AYAs with cancer are emerging in clinical settings in an effort to meet this critical need but remain under-researched. The goal of this pilot study is to examine the feasibility and acceptability of a telehealth peer support group intervention for AYAs with cancer. Findings from this study have the potential to impact psychosocial care of AYA oncology patients and programs and inform implementation of evidence-based care consistent with the Standards for Psychosocial Care for Children with Cancer and Their Families.

This study has several notable strengths, including important research and clinical innovations. Psychosocial interventions have moved to virtual platforms after the COVID-19 pandemic, and although this modality for care delivery is increasingly used, it remains largely untested. There is a wide research-practice gap in which the scientific evidence for telehealth interventions lags far behind its adoption in clinical practice [45]. This innovative project is timely in addressing an important gap in the literature, especially among AYAs with cancer, a unique and under-researched population. Additionally, this study employs a mixed-methods design [46, 47]. It centers AYAs’ voices by including patient stakeholder interviews and includes quantitative measures which have been limited in the extant research [4].

The group intervention itself has several noteworthy clinical innovations, including use of patient narratives and peer support. The model is patient centered in that discussion topics are prioritized by the patients in attendance, and group attendance is flexible to accommodate patient location (e.g., patients can join remotely from home, an infusion chair, or the inpatient unit) and sessions missed due to conflicting appointments or illness. The group is designed to be inclusive by including patients both on and off treatment rather than survivors only and patients with a heterogeneity of medical diagnoses. Importantly, separate high school and AYA groups address the diversity of experiences among AYAs and attend to specific developmental needs for patients across the AYA age spectrum.

This study has several limitations as well as potential practical and operational challenges and considerations. First, this is a small, single-site pilot study without a comparison group, and generalizability of findings for a single-site study is limited. Recruiting a diverse sample may also be challenging. Nonetheless, this study is an important first step and will serve as formative groundwork for future studies to test this intervention in a multi-site randomized controlled trial. Second, groups will include a heterogeneity of diagnoses and treatment phases; sample size will prohibit meaningful examination of potential differences across diagnoses and treatment phases. This will be important to examine in future larger studies. Diversity of experiences may be beneficial as this group intervention is intended to be broadly applicable to AYAs with cancer on and off treatment. Third, groups are limited to English-speaking participants. Active efforts are underway at our institution to obtain simultaneous interpretation for group interventions. Fourth, because AYAs self-select into groups, this may affect the representativeness of our sample, and this study carries risk of selection bias. We will not be able to collect data (e.g., feedback about barriers, reasons for nonparticipation) for AYAs who are not interested or referred to the group. This is another important future direction for research. We will track reasons for nonparticipation for AYAs who are referred to group but decline/do not enroll. Additionally, patients’ lack of awareness of availability of behavioral health services is often a barrier to receiving services. Some patients and families may not be aware of groups (e.g., patients who are seen less frequently at SCH, are further out from treatment, or who may be viewed by providers as less likely to want to participate in a group) precluding their participation, which may also affect representativeness of participants. Strong efforts will be made to increase patient and family awareness of the availability of the groups. Fifth, some group members have enrolled in prior cycles of group and are considered “repeaters,” which may also contribute to selection bias. As such, their baseline is not a true baseline. We will take this into consideration as we analyze the data. This observation suggests that some AYAs find continued benefit from the intervention prompting them to repeat group participation, which has interesting and important clinical implications. Finally, use of the adapted internally developed measure of acceptability was a pragmatic decision and includes items that assess both intervention acceptability and satisfaction. A future direction is to more clearly measure these constructs separately, such as by adapting the theoretical framework of acceptability questionnaire to assess acceptability of our telehealth group intervention for AYAs with cancer at the current and other treatment centers [48].

The next step in this program of research is to use findings on feasibility and acceptability to inform and make modifications to the intervention and refine a group curriculum that may serve as an exemplary model of care for increasing patient access to psychosocial standards of care for social interaction and psychosocial interventions at pediatric oncology sites. Future goals include evaluating the intervention’s effectiveness in an adequately powered randomized controlled trial. Development and testing of an evidence-based telehealth peer support group intervention for AYAs with cancer that improves psychosocial outcomes will meet a significant need for this vulnerable population.

